## Abstract

**Background:**

Vulvar Paget disease is a rare skin disorder, which is most common in postmenopausal Caucasian women. They usually present with an erythematous plaque that may show fine or typical “cake icing” scaling or ulceration that may cause itching, pain, irritation, or a burning sensation. Although most cases are noninvasive, vulvar Paget disease may be invasive or associated with an underlying vulvar or distant adenocarcinoma. The histological evidence of so-called “Paget cells” with abundant pale cytoplasm in the epithelium confirms the diagnosis. The origin of these Paget cells is still unclear. Treatment of choice is wide local excision with negative margins. Obtaining clear surgical margins is challenging and may lead to extensive and mutilating surgery. Even then, recurrence rates are high, ranging from 15% to 70%, which emphasizes the need for new treatment options. A number of case reports, retrospective case series, and one observational study have shown promising results using the topical immune response modifier imiquimod.

**Objective:**

This study aims to investigate the efficacy, safety, and immunological response in patients with noninvasive vulvar Paget disease using a standardized treatment schedule with 5% imiquimod cream.

**Methods:**

Topical 5% imiquimod cream might be an effective and safe treatment alternative for vulvar Paget disease. The Paget Trial is a multicenter observational cohort study including eight tertiary referral hospitals in the Netherlands. It is ethically approved by the Medical-Ethical Committee of Arnhem-Nijmegen and registered in the Central Committee on Research Involving Human Subjects (CCMO) Register by as NL51648.091.14. Twenty patients with (recurrent) noninvasive vulvar Paget disease will be treated with topical 5% imiquimod cream three times a week for 16 weeks. The primary efficacy outcome is the reduction in lesion size at 12 weeks after end of treatment. Secondary outcomes are safety, immunological response, and quality of life. Safety will be assessed by evaluation of adverse events and tolerability of treatment. To evaluate the immunological response, various immunological markers will be tested on biopsy specimens taken before, during, and after treatment. Quality of life will be assessed with three questionnaires taken before, during, and after treatment.

**Results:**

First results are expected in the summer of 2018.

**Trial Registration:**

ClinicalTrials.gov NCT02385188; https://clinicaltrials.gov/ct2/show/NCT02385188 (Archived by WebCite at http://www.webcitation.org/6sXygHuhP).

## Introduction

Cutaneous Paget disease was first described in a series of patients with nipple ulceration and an underlying breast carcinoma. This became known as mammary Paget disease (MPD) [1]. When the same condition was reported on the scrotum and vulva, these were named extramammary Paget disease (EMPD) [2,3].

The presence of so-called Paget cells in the basal layers of the epithelium is pathognomonic for this rare disease. The origin of these large cells with abundant clear, pale cytoplasm, which often contain mucin, remains unclear. The most common hypothesis is that Paget cells originate from adnexal structures, such as apocrine glands or multipotent stem cells in the basal layer of the epidermis [4,5]. Other theories suggest the anogenital area contains mammary-like glands or that Toker cells, also seen in the nipple in mammary Paget disease, are precursor cells for EMPD [6-8].

The incidence rate of EMPD is 0.11 per 100,000 person-years, based on an epidemiological study with data of the Netherlands Cancer Registry [9]. Vulvar Paget disease (VPD) causes pain, itching, or a burning sensation, and a skin lesion, which can be described as a scaling, erythematous plaque that sometimes shows ulceration. VPD typically presents in postmenopausal Caucasian women [8].

Vulvar Paget disease can be divided into primary VPD, which is cutaneous, and secondary VPD, which is noncutaneous. Textbox 1 illustrates the different types of VPD [10].

Vulval Paget disease is associated with different malignancies, mainly an underlying vulvar, intestinal, or urological malignancy, and breast cancer. Approximately 20% of patients are reported to have an associated malignancy in their history. Therefore, screening for underlying carcinoma is advised, although there is no evidence for screening and no consensus on the extent of the additional diagnostic procedures [11,12].

Historically, the treatment of choice for VPD is wide local excision with clear margins, which is not always easy to realize on the vulva. Because Paget cells are found widely spread throughout the anogenital area, it is almost impossible to obtain clear surgical margins [13,14]. The recurrence rates of VPD are high: 15% to 70% independent of margin status. The risk of recurrence is highest in the first year after treatment [15]. To improve obtaining clear surgical margins, Mohs microsurgery has been evaluated for treatment of VPD. In Mohs microsurgery, the lesion is excised and the entire margin is examined immediately [16]. In case the margin is not clear, the excision is repeated, enlarging the circumference until the margins are clear. This technique may lead to lower recurrence rates [17]. However, large vulvar excisions may require plastic reconstruction.

Extensive vulvar surgery can cause permanent mutilation and functional impairment [18-22]. To address this problem, alternative treatment options such as photodynamic therapy, radiotherapy, chemotherapy, laser treatment, and recently topical 5% imiquimod cream have been used in patients with VPD with varying degrees of success [23-30].

Topical 5% imiquimod cream is an immune response modifier. It binds to toll-like receptor 7, inducing an innate and cell-mediated immune response [31]. It has antiviral and antitumor properties and is registered for the treatment of condylomata acuminata, actinic keratosis, and superficial basal cell carcinomas. Imiquimod also has shown to be effective for human papilloma virus-induced usual vulvar intraepithelial neoplasia [32,33]. The mechanism of action of imiquimod and local immunity in VPD are not known.

Different types of vulvar Paget disease.**Primary EMPD (cutaneous)**Type 1a: associated with noninvasive, intraepithelial diseaseType 1b: associated with invasive diseaseType 1c: associated with an underlying adenocarcinoma**Secondary EMPD (noncutaneous)**Type 2: EMPD originates from intestinal adenocarcinomaType 3: EMPD originates from urothelial carcinoma

More recently, a number of case reports, case series, and one observational trial that reported on the use of topical 5% imiquimod cream for VPD showed that imiquimod may be an effective treatment option [34,35]. A systematic review also concluded it is an effective alternative for VPD [36]. However, most studies described limited numbers of patients, various treatment schedules, and short follow-up periods. Therefore, it is impossible to pool data from previous studies to make final conclusions about the efficacy. The authors of the systematic review also mentioned the risk of publication bias: only positive results may be published retrospectively [36].

### Objective

The objective of this study is to assess the clinical efficacy, safety, and local immunity of topical 5% imiquimod cream in patients with noninvasive VPD.

## Methods

### Study Design

This study is a multicenter, prospective, open-label observational cohort study in patients with histologically proven, noninvasive VPD. Patients will be treated with topical 5% imiquimod cream three times a week for 16 weeks, with follow-up of one year after the end of treatment.

### Study Setting

Because VPD is rare, with an estimated incidence of four to seven cases per year in the Netherlands, the trial will be carried out in seven tertiary referral hospitals with a vulvar clinic in the Netherlands. Vulvar clinics are outpatient multidisciplinary clinics with participation of both gynecologists and dermatologists who are specialized in disorders of the vulva.

Participating centers are Antoni van Leeuwenhoek, Netherlands Cancer Institute, Amsterdam; Catharina Ziekenhuis, Eindhoven; Erasmus Medical Center, Rotterdam; Leiden University Medical Center; Radboudumc, Nijmegen; University Medical Center Groningen; and University Medical Center Utrecht.

### Participants

All patients with histologically proven noninvasive cutaneous VPD visiting or referred to a participating clinic will be asked to participate in this study. We estimate to include one patient per center per year because of the rarity of the disease.

Inclusion criteria are noninvasive VPD (primary or recurrence after earlier surgery or imiquimod treatment more than 6 months previously), age 18 years and older, and willing and able to comply with the protocol and provide informed consent in accordance with institutional and regulatory guidelines. Most patients are expected to be elderly, postmenopausal women, who may suffer from comorbidities. All patients will be instructed on how to apply the imiquimod cream by their clinician, according to the leaflet provided by the manufacturer, and using a mirror. If the patient is physically unable to apply the cream, a health care provider (eg, a nurse at the nursing home or via domiciliary care) will receive written instructions. If the patient consents, a printed photograph in which the affected skin is marked will be provided. Main exclusion criteria are current invasive VPD, underlying adenocarcinoma, and treatment of the vulva with topical 5% imiquimod cream during the last 6 months.

### Sample Size

Based on the estimated incidence of VPD in the Netherlands, viability is set at 20 inclusions. Our sample size considerations are based on the response rate. The primary outcome variable is the response at 12 weeks after end of treatment with topical 5% imiquimod cream. The only observational study on this topic, at time of conception of this trial, reported a response in 9 of 10 women [35]. Assuming a complete response rate of 80%, a cohort size of 20 patients is sufficient to estimate the complete response rate with a standard error of 9%, using the normal approximation for the binomial distribution. Because we presume that the dropout rate will not exceed 20%, a maximum of 25 patients will be included. When 20 patients have been treated with topical 5% imiquimod cream for at least 8 weeks, we will stop recruitment.

### Study Intervention

All patients will be treated with topical 5% imiquimod cream three times a week for 16 weeks. This treatment schedule is based on the treatment schedule for condylomata acuminata and on a previous randomized controlled trial of imiquimod 5% for usual vulvar intraepithelial neoplasia [31,33]. The healthy skin around the visible lesion can be protected with an indifferent basic ointment. Patients are allowed to use topical 3% lidocaine in Vaseline ointment if they experience pain at the application site. There must be a 1-hour interval between the application of different topical agents. Patients are also allowed to use paracetamol. In case of severe pain, when paracetamol and 3% lidocaine ointment are insufficient, it is permitted after consultation with the clinician to stop the treatment with topical 5% imiquimod cream for one week at a time. Patients are allowed to stop/delay treatment for a total of 3 weeks within the assigned treatment period.

**Table 1 table1:** Study schedule presenting an overview of all study activities.

Study activities		0 w	Baseline	4 w	10 w	16 w	28 w	40 w	52 w	68 w
**Before treatment**										
	Mapping and mammography	X								
	Written informed consent	X								
	Require histological samples (incl. mapping) and mammography results from referring hospital	X								
**Imiquimod 5% cream**			Start			Stop				
	Consultation by phone				X					
	Consultation at outpatient clinic of involved research clinic, containing:		X	X		X	X	X	X	X
	Vulvar examination, measurement and photo documentation		X	X			X			X
	VAS score		X	X	X	X	X	X	X	X
	Tolerability questionnaire			X	X	X				
	Biopsy	X		X			X			
	EQ5D		X	X			X			
	DLQI		X	X			X			
	FSDS		X	X			X			
	Review patient diary			X	X	X				

In case of a suspected secondary bacterial infection, fucidin cream or ointment 20 mg/g will be prescribed. The patient will apply the fucidin cream or ointment three times a day, according to the prescription. No other local products than imiquimod cream, lidocaine, indifferent moisturizers, or fucidin are allowed to be applied at the lesion site. On an individual basis, other topical products will be considered as a protocol violation.

### Study Schedule

Patients will visit the clinic seven times during the study; the final visit will be 1 year after the end of treatment (Table 1). One consultation will take place by telephone. During these consultations, pain will be measured by means of the visual analog scale (VAS) score for pain. Pain, burning, and itching will be asked on a four-point Likert scale. During the visits, the clinical response will be evaluated by vulvar examination and bidimensional measurement of the visible lesions. The histological effect will be assessed by pathological assessment of the presence of Paget cells in the biopsy sample(s) taken 12 weeks after the end of treatment. All biopsy samples taken before, during, and after treatment will be taken around the same location. The site of the first biopsy is most likely the most evident lesion, causing a clinically visible lesion. The site of this biopsy will be recorded in the case report file to ensure other biopsies will be taken at the same area. Quality of life will be assessed before, during, and after treatment using three questionnaires on general health (EQ-5D), dermatological quality of life (Dermatology Quality of Life Index [DLQI]), and (if applicable) sexual functioning (Female Sexual Distress Scale [FSDS]).

Safety will be evaluated by documentation of all adverse effects, recorded by the clinician and by the patient in the patient diary.

The immunological effect will be assessed by comparing the results of additional immunohistochemistry stains performed on all three samples taken around the same location at baseline, 4 weeks after start of treatment, and 12 weeks after end of treatment. All biopsies will be taken at approximately the same location to ensure the local microenvironment is as similar as possible in all samples. There are limited data on the tumor microenvironment in VPD; we are currently performing a separate pilot study to investigate the parameters in the immune infiltrate in VPD. We are investigating which immune cells are present in VPD, and will use this knowledge to further explore which immune cells respond to the topical imiquimod cream and the role they play in the origin and treatment of VPD. The results of this separate pilot study will be used to decide which markers will be investigated in the samples collected in the Paget Trial.

### Study Endpoints

The main study outcome is clinical response. This will be assessed by determination of the reduction in lesion size 12 weeks after the end of treatment. This will ensure any local skin effects caused by treatment will be healed at time of examination. All measurements during the study will be conducted by the same trained and experienced local clinician. Photographs for documentation will be taken with a ruler alongside the lesions. The comparison between the lesion size at the start of treatment and 12 weeks after the end of treatment can lead to the following outcomes:

Complete response: defined as disappearance of the lesion and histological confirmation of disappearance;Partial response: defined as decrease by ≥50% of total lesion size;No response: defined as <50% decrease of total lesion size; orProgressive disease: defined as ≥25% increase of total lesion size or progression into invasive disease and/or adenocarcinoma.

Secondary outcomes are the safety, quality of life, and the assessment of local immunological response. These outcomes will be assessed according to the following criteria:

Safety: all adverse events that occur during the study will be collected by the clinician at every consultation (at the clinic or via telephone) and by the patient using a standardized patient diary.Quality of life: results of the three questionnaires (EQ-5D, DLQI, and, if applicable, FSDS) taken before, during, and after treatment will be compared.

Local immunological response will be assessed by a set of markers, to be determined, in tissue samples obtained by vulvar biopsy before, during, and after treatment.

### Statistical Analysis:

An intention-to-treat (ITT) and per protocol (PP) analysis will be performed. The population included in the ITT analysis is defined as all patients that have started treatment with topical 5% imiquimod cream. The PP analysis will include patients that have completed treatment with topical 5% imiquimod cream according to protocol. Two-tailed *P* values <.05 will be considered statistically significant. Our primary study parameter is the clinical response to topical 5% imiquimod cream. Twelve weeks after the end of treatment, the clinician will examine the vulva of the patient and assign the patient in one of the response categories as defined previously. Estimates of the percentage responders per response category will be presented with corresponding 95% confidence intervals. The relation between treatment duration and dose versus response will be explored. Safety will be analyzed in a descriptive manner, presenting all adverse events (local and systemic) in all participants treated with topical 5% imiquimod cream. Also, the use of painkillers, lidocaine ointment, and discontinuation of treatment will be reported.

Quality of life will be assessed by three questionnaires. The EQ-5D results will be converted to the crosswalk index values, using the Crosswalk Index Value Calculator [37]. The DLQI results will be categorized according to the instruction manual, ranging from “no effect at all on patient’s life” to “extremely large effect on patient’s life” [38]. The result of the FSDS is the sum of the answers. Descriptive statistics will be used to present the change outcomes during treatment versus before treatment, and after treatment versus before treatment. A subanalysis of responders and nonresponders will be conducted.

The immunological results will be counted and compared between the different biopsy samples. These data will be reported in a descriptive manner.

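### The DLQI is the only questionnaire whose stated result is a set of categories, so its change is described less precisely than the collected answers allow

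*Protocol article*

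**What the plan says.** The Statistical Analysis section of the protocol article fixes a form for each of the three questionnaires:

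- EQ-5D: "The EQ-5D results will be converted to the crosswalk index values", which is a number.
- DLQI: "The DLQI results will be categorized according to the instruction manual". The article names only the two end labels, from no effect to an extremely large effect on the patient's life.
- FSDS: "The result of the FSDS is the sum of the answers", which is a number.

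One sentence then covers all three: "Descriptive statistics will be used to present the change outcomes during treatment versus before treatment, and after treatment versus before treatment". It is followed by "A subanalysis of responders and nonresponders will be conducted".

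Table 1 schedules the DLQI at baseline, week 4 and week 28. Week 28 is 12 weeks after the end of the 16-week treatment. Study Endpoints gives the rank of the outcome: "Secondary outcomes are the safety, quality of life, and the assessment of local immunological response". Nowhere does the article name a numeric DLQI score, or a change in one, as something to be summarised.

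**The concern.** The stated aim is within-patient change, and categories are a blunt tool for that. Two patients with very different changes can fall in the same cell of a before-and-after table, and two with nearly the same change can fall in different cells, depending only on where they started relative to a cut. The other two questionnaires avoid this because they stay numeric, and the article gives no reason for treating the DLQI differently.

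At stake is how well the trial can describe skin-related quality of life. The DLQI is its only dermatology-specific questionnaire. The Discussion gives the scarcity of data on how the disease affects daily life as the reason for collecting quality of life at all. The cohort is about 20, and the planned split by response makes the groups smaller.

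**Working it through.** **The plan's own figures.** The only precision figures in the article are in Sample Size, and they reproduce:

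- Standard error of the complete response rate: √(0.80 × 0.20 / 20) = 0.0894, stated as 9%.
- Maximum enrolment with 20% dropout: 20 / (1 − 0.20) = 25, as stated.

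Neither concerns the DLQI, for which the article states no figure.

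**Size of the subgroups.** If responder means complete responder, the assumed 80% rate gives 20 × 0.80 = 16 responders and 20 − 16 = 4 others. If partial response also counts, the second group can only be the same size or smaller.

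**What categories do to one patient's change.** Take a 0–30 score with cuts at 2, 6, 11 and 21, each being the lowest score of the next band (range and cuts assumed):

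- 20 before and 12 after: an 8-point fall, recorded as no change.
- 11 before and 10 after: a 1-point fall, recorded as a full category.

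**Illustration A: a cohort of 20.** All inputs are assumptions: score 0–30, SD 5, within-patient correlation 0.6, true change 3 to 5 points, baseline mean 6 to 14, five bands, with cuts either equal (6/12/18/24) or unequal (2/6/11/21).

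Relative information = (mean paired t on band number / mean paired t on score)².

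- Change in bands keeps about 55% to 92% of the information in numeric change. A repeat run gave 53% to 93%, so the ends are good to about 2 percentage points.
- On the scale of 20 patients this is 20 × 0.55 = 11 to 20 × 0.92 = 18.4.
- 28% to 57% of patients stay in the same band.
- 3% to 21% stay in the same band although their score changed by at least 3 points.

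**Illustration B: a different model.** Inputs, again assumed: normal score, mean shift 0.5 SD, equal-probability bands, correlation ρ of 0.5 or 0.7.

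Relative efficiency = (mean/SD of band change)² / (mean/SD of score change)².

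The denominator is 0.5² / [2(1 − ρ)], which is 0.25 for ρ = 0.5 and 0.25 / 0.60 = 0.417 for ρ = 0.7.

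| Bands | ρ | Relative efficiency | × 20 patients | Same band |
|---|---|---|---|---|
| 3 | 0.5 | 0.653 | 13.1 | 47% |
| 3 | 0.7 | 0.544 | 10.9 | 54% |
| 4 | 0.5 | 0.746 | 14.9 | 37% |
| 4 | 0.7 | 0.652 | 13.0 | 44% |
| 5 | 0.5 | 0.796 | 15.9 | 30% |
| 5 | 0.7 | 0.717 | 14.3 | 36% |
| 6 | 0.5 | 0.826 | 16.5 | 26% |
| 6 | 0.7 | 0.754 | 15.1 | 31% |

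Both models show a loss in every scenario. Its size ranges from slight to substantial, depending on the cuts and on where patients start.

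**The case against.** The strongest reply is that the article never says change will be computed on categories. The sentence on change covers all three questionnaires together and does not name the DLQI variable. Nothing forbids reporting the score as well, and the article condenses a fuller protocol in which the score may be tabulated. This softens the point but does not remove it. The article did not leave the DLQI's form open: it stated one form for each questionnaire, and the DLQI's is categories.

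A second reply is that the manual's categories are a legitimate way to make a score interpretable. That stands, and it is a reason to keep them beside the score.

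A third reply is that the percentages come from ratios of paired t statistics, while no DLQI test is planned. That also stands. They measure how precisely an average change can be described, and should not be read as lost power or as patients lost.

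A reader might go further and infer that banding throws away data already collected. The article does not support that. The questionnaire answers remain, the total can be tabulated at any time, and the loss lies only in analysis and reporting. Nor does the point extend to EQ-5D or FSDS, which are already numeric.

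**Conclusion.** The point holds as a minor improvement to a stated method. As written, the DLQI result is a category, while the purpose is to describe change and the two companion questionnaires stay numeric. The direction of the loss follows from the banding itself. The size, roughly 55% to 92% of the information kept, rests wholly on an assumed score range, SD, correlation, expected change, baseline level and cut-points, none of which the article gives, and it is illustrative only.

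The consequence is small. The DLQI is one of three questionnaires within one of three secondary outcomes, the analysis is descriptive, and the primary outcome, sample size and safety reporting do not depend on it.

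**What to change.** Add one sentence to the analysis plan: the DLQI total score, and its paired change from baseline to week 4 and from baseline to week 28, will be summarised as a mean or median with a measure of spread or a 95% confidence interval; the manual's categories will be shown in addition, as an aid to interpretation. Use the same numeric summary for the DLQI in the responder and nonresponder subanalysis. Leave EQ-5D and FSDS as they are.

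The cost is that sentence and a few table rows. No new data, visits or patient burden are needed. When the article was written, 17 patients were taking part and first results were still awaited, so the change could be made before analysis.
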